## Abstract

**Background:**

Currently, there still is no treatment that eliminates tinnitus in all patients. Recent studies have shown that Tinnitus Retraining Therapy (TRT) significantly improves quality of life for tinnitus patients. Also, several studies have reported that transcranial Direct Current Stimulation (tDCS) has a positive effect on attention, working memory, long-term memory and other cognitive processes. The aim of this randomised placebo-controlled double-blind study is to evaluate the added effect of tDCS to TRT in chronic tinnitus patients. To our knowledge, this is the first study to combine both methods.

**Methods:**

Patients with chronic, non-pulsatile tinnitus will be randomised in two treatment groups: TRT and real tDCS versus TRT and sham tDCS. Evaluations will take place at baseline before therapy starts, at the end of the TRT and 3 months after therapy starts. The Tinnitus Functional Index will be used as the primary outcome measurement. Secondary outcome measurements will be the Visual Analogue Scale of Loudness, Hospital Anxiety and Depression Scale (HADS), Hyperacusis Questionnaire, psychoacoustic measurements and Event-related potential (ERP).

**Discussion:**

To our knowledge this is the first study to combine TRT and tDCS. The objective is to evaluate whether tDCS can provide faster and/or more relief from the annoyance experienced in chronic tinnitus patients’ daily lives. The advantage of the study is that it is double-blind and placebo-controlled.

**Trial registration:**

The present study protocol was registered on 31 October 2014 at Clinicaltrials.gov: NCT02285803.

## Background

Tinnitus is the perception of sound without the occurrence of a corresponding external sound source. Approximately 25.3 % of the US population experience some tinnitus and 7.9 % suffer from frequent tinnitus [1]. Currently, there is still no treatment that totally eliminates tinnitus in all patients. Therefore, the goal is to change the reaction to tinnitus and thus reduce the impact of tinnitus on the patient’s daily life. The type of counselling that tries to achieve this goal is called Tinnitus Retraining Therapy (TRT). Early studies have shown that 82 % respond positively to TRT [2]. TRT is comprised of two components: counselling and sound enrichment. Counselling is a one-on-one conversation between the patient and the audiologist or counsellor. A family member may be involved at the patient’s request. The counselling is based on the Jastreboff neurophysiological model [3]. Counselling will educate the patient on the working mechanism of the ear and tinnitus and promote adaptive coping behaviours. The second important aspect of TRT is sound enrichment. This can be achieved through a noise masker or even background noise in the environment. Sound enrichment results in partial or complete masking of the tinnitus, allowing the patient to ignore or transfer it to the subconscious. Philips et al. (2010) emphasised the importance of using low-level noise instead of completely masking the tinnitus to achieve down-regulation [4].

Transcranial Direct Current Stimulation (tDCS) is a form of neuromodulation in which a low current is applied to the brain by means of two electrodes: the anode placed on the dysfunctional site and the cathode placed on a ‘silent’ part of the body. Nowadays, mostly bifrontal tDCS is applied in tinnitus patients with the anode and cathode placed on the right and left dorsolateral prefrontal cortex (DLPFC) respectively. However, Martin et al. suggested placing the cathode on the right upper arm and the anode on the left DLPFC to prevent cathode-related inhibitory effects at the cortical site [5]. Research has shown that tDCS can provide temporary relief from tinnitus in 39.5 % of tinnitus patients [6]. In addition, previous studies have shown that tDCS has a beneficial effect on numerical competence [7] and working memory in depressed persons [8]. It also has also been reported beneficial to learning and memory in persons with a brain injury [9].

The aim of the present study is to evaluate the additive effect of tDCS to TRT. The idea is that tDCS would prime the central nervous system and thus create a stronger and faster learning effect for coping with tinnitus. This setup was based on the research of Martin et al. [10]. Their research showed that performance on a cognitive task could be improved by giving tDCS during the task [10]. The timing of tDCS was also found to be important. Furthermore, Martin et al. [11] found that tDCS simultaneously presented with a cognitive training task led to better within-session skill, with a significant difference found between conditions the following day when compared to presentation of tDCS prior to the cognitive training. Therefore, Martin et al. suggested the combination of tDCS with a rehabilitation protocol to improve the effect of the protocol [11].

## Methods

The present study is a randomised placebo-controlled double-blind trial in order to find out if tDCS adds value to TRT in chronic tinnitus patients. Patients will be referred by the ear, nose and throat (ENT) department of the Antwerp University Hospital and will be randomised in group A (real tDCS) or group B (sham tDCS).

### Ethics

Written consent will be obtained from every patient. The study protocol was approved by the ethical committee of the Antwerp University Hospital on 27 October 2014 with protocol number EC14/40/406 (Clinaltrials.gov: NCT02285803).

### Inclusion and exclusion criteria

The patient must meet specific criteria during consultation with the ENT before inclusion and randomisation. The appropriate examinations will be performed to make sure the patients meet the exclusion and inclusion criteria. During the study, the patient has the right to leave the study at any time. The occurrence of severe adverse events also can lead to discontinuation of the study.

The inclusion criteria are as follows:Duration of (worsening of) tinnitus between 3 months and 4 yearsMinimum age of the patient is 18 years oldMaximum loudness of tinnitus on the Visual Analogue Scale (VAS) ≥ 4Tinnitus Functional Index (TFI) score ≥ 25

A patient is excluded from the study for the following reasons:Pulsatile tinnitusAuditory thresholds > 70 decibels hearing level (dBHL)PregnancyTreatment of psychiatric disorder by a psychiatristPacemaker or defibrillatorAcoustic neuromaHistory of cerebrovascular accidentMénière’s diseaseWhiplashEpilepsyChange of medication use

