#### Transcranial Direct Current Stimulation (tDCS)

During every TRT session, the patient will receive tDCS during the counselling. There are two groups: one will receive ‘real’ tDCS and the other will receive ‘sham’ tDCS. The latter is the placebo group. Direct current is transferred by means of 2 saline-soaked pairs of surface sponge electrodes (35 cm^3^) and delivered by a specially developed, battery-driven, constant current neuroConn stimulator (neuroConn, Ilmenau, Germany) with a maximum output of 10 mA. The anode (positive electrode) will be placed on the right DLPFC (Brodmann area 9/46), and the cathode (negative electrode) will be placed on the left upper arm according to the 10–20 international system for electroencephalogram (EEG) electrode placement. The extracephalic placement of the cathode was chosen because of the reduced risk of current flowing from one electrode to the other, and as a consequence, the actual current could stimulate a deeper and wider brain area. Settings for both groups are described in Table 1. For the ‘real’ tDCS group, a constant current of 2 mA will be applied for 20 minutes with a fade-in and fade-out of 10 s. The ‘sham’ tDCS group will receive a tDCS session of only 10 s with a current of 1 mA. Patients in the sham group will experience the same tingling effect at the beginning of the tDCS as those in the real tDCS group, but no real stimulation will take place. Both the patient and investigator are blinded to the intervention type due to a five-digit code that can be entered in the study mode of the tDCS device that will be encoded sham or active tDCS stimulation. The five-digit codes were randomised and supervised by a third party.

**Table 1 Tab1:** Settings for real Transcranial Direct Current Stimulation (tDCS) and sham tDCS

	Real tDCS	Sham tDCS
Current	2 mA	1 mA
Fade in/out	10 s	10 s
Duration	1200 s	10 s

The settings of tDCS are chosen so the patient would not notice a difference and they are blinded for the fact that they are randomised in the placebo or the real treatment group

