## Discussion

Currently, there is no specific treatment to cure tinnitus in all patients. Although tDCS is a known treatment for tinnitus, it has shown only limited relief in 39.5 % of patients [6]. However, previous studies have shown that TRT results in tinnitus relief for 82 % of the study population [2]. This is a long-term process, and our goal of this study is to evaluate if tDCS can provide faster and/or more relief of the annoyance experienced in patients’ daily lives.

The advantage of the study is that it is double-blind and placebo-controlled. The fact that we compare sham and real tDCS will rule out the placebo effect of tDCS. The study is also based on the literature: a recent study showed that tDCS presented simultaneously with a cognitive training task led to better within-session skill, with a significant difference found between conditions the following day when compared to presentation of tDCS prior to the cognitive training. The authors suggested combining tDCS with rehabilitation protocols [11]. To our knowledge, this is the first study to combine both study methods.

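### Previous tDCS is not an exclusion, so patients who already know the stimulation may guess their allocation, in either arm, on a self-reported primary outcome

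*Protocol article*

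**What the plan says.** All references are to the Protocol article.

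- **Inclusion and exclusion criteria.** There are four inclusion criteria: tinnitus, or a worsening of it, for 3 months to 4 years; age; VAS loudness; and TFI of at least 25. The exclusions are introduced by "A patient is excluded from the study for the following reasons". Eleven follow: pulsatile tinnitus, thresholds above 70 dBHL, pregnancy, psychiatric treatment, pacemaker or defibrillator, acoustic neuroma, cerebrovascular accident, Ménière's disease, whiplash, epilepsy and change of medication. Neither list mentions earlier tDCS or any other brain stimulation.
- **Background.** "Nowadays, mostly bifrontal tDCS is applied in tinnitus patients".
- **Discussion.** "Although tDCS is a known treatment for tinnitus, it has shown only limited relief in 39.5 % of patients". The same section says that comparing sham with real stimulation removes the placebo effect of tDCS.
- **Transcranial Direct Current Stimulation (tDCS).** In the real arm, "a constant current of 2 mA will be applied for 20 minutes with a fade-in and fade-out of 10 s". The sham arm "will receive a tDCS session of only 10 s with a current of 1 mA". The stated basis for the patient blind is "Patients in the sham group will experience the same tingling effect at the beginning of the tDCS", and the note to Table 1 adds "The settings of tDCS are chosen so the patient would not notice a difference". A five-digit device code conceals the allocation.
- **Tinnitus Retraining Therapy** and **Tinnitus Functional Index (TFI).** Each patient has about six sessions, with tDCS at each. The primary outcome is a self-completed questionnaire scored 0 to 100.

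**The concern.** On the printed criteria a patient who has already had tDCS for tinnitus is eligible. The article's own description of tDCS, together with referral from a university hospital ENT department and up to 4 years of symptoms, makes such a patient conceivable.

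The device code hides the allocation but not the sensation. A naive patient who feels a short tingle has no standard against which to judge it. A patient who has sat through a full session does, and can apply it at about six visits. If such patients guess their arm, those who believe they are on sham may rate their improvement lower, and those who believe they are on real stimulation may rate it higher. Both shifts favour real tDCS. At stake is the claim that the sham control separates stimulation from expectation, in a trial of 24 patients whose only primary outcome is self-rated.

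**Working it through.** The plan states no figure on this point, so there is nothing to reproduce. The check is textual, followed by an illustration of size.

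**Textual check**

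1. Is previous tDCS barred? No. It appears in none of the eleven exclusions and none of the four inclusion criteria.
2. Does the article treat tDCS as something tinnitus patients receive? Yes, in the Background and the Discussion.
3. Do the two conditions differ in ways an experienced patient might notice? Current is 2 mA against 1 mA, and duration is 1200 s against 10 s, with the same 10 s fades.
4. Is the outcome open to expectation? Yes, the TFI is self-reported.
5. Is recognition limited to one arm? Nothing says so. A patient who can tell that sham is not the real thing can also tell that real stimulation is.

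**Illustration of size**

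Inputs from the Protocol article (Sample size calculation): N = 24, SD 20, and a meaningful TFI reduction of 13 points. Assumptions, none given in the article: equal allocation (12 per arm); a share q of each arm that has had tDCS and recognises the condition; and a shift b of 10 to 20 TFI points (0.5 to 1 SD) in the reported improvement of those patients.

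- Chance of at least one experienced patient among 12 on sham: 1 − (1 − q)^12
- Bias if only sham is recognised: q × b
- Bias if both conditions are recognised, with equal and opposite shifts: 2 × q × b

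| q (assumed) | At least one of 12 on sham | Bias, sham recognised only | Bias, both recognised |
|---|---|---|---|
| 0 | 0 | 0 | 0 |
| 5 % | 46 % | 0.5-1 points | 1-2 points |
| 10 % | 72 % | 1-2 points | 2-4 points |
| 20 % | 93 % | 2-4 points | 4-8 points |

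In whole patients, one recogniser among 12 moves the sham mean by 10/12 = 0.8 to 20/12 = 1.7 points, and two move it by 1.7 to 3.3 points.

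**Scale**

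The standard error of a simple difference in means at 12 per arm is 20 × √(2/12) = 8.2 points. A bias of 1-2 points is 12 % to 24 % of that, and 8 % to 15 % of the 13-point benchmark. A repeated-measures analysis can be more precise. With an assumed correlation of 0.8, a change score has SD 20 × √(2 × 0.2) = 12.6 and standard error 12.6 × √(2/12) = 5.2, so 1-2 points is 19 % to 39 % of it. The bias is modest beside random error on either basis, but unlike random error it does not average out.

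**The case against.** **Exposure is not shown.** The Background sentence is mainly about electrode placement, and the 39.5 % in the Discussion is a response rate from a cited study. Neither shows that patients of this ENT department have had tDCS. This stands: q may be zero, and then every figure above vanishes.

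**Recognition is not shown.** The article asserts that the initial tingling is the same and that patients will not notice a difference. Earlier experience may also transfer poorly, since the Background describes mostly bifrontal stimulation whereas this trial places the cathode on the upper arm and stimulates during counselling. This also stands, as far as it goes. There are no data either way, so the point can say only that experienced patients may guess.

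**The article is condensed.** A fuller protocol may record treatment history. That is fair for baseline data, but weaker for eligibility: the list is presented as the reasons for exclusion and is detailed enough to include whiplash.

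Some stronger readings are tempting but unsupported:

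- *Only the sham arm is unblinded.* A reader might infer this because the sham looks like the odd one out. But a patient who knows a full session may recognise either condition.
- *The trial loses power because earlier recipients are non-responders.* A reader might infer this from the TFI entry threshold. But the Background speaks of temporary relief, so a past responder whose tinnitus returned is equally eligible. A calculated power loss would need every experienced patient to gain nothing, which nothing in the article supports.

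**Conclusion.** The point holds in a limited form. The criteria admit patients with previous tDCS, the article describes tDCS as a known tinnitus treatment, and the patient blind depends on a brief, weak sham passing for a long session. Experienced patients in either arm may therefore guess their allocation. The likely direction of bias on the TFI is towards real tDCS, and the statement that the sham control removes the placebo effect is less secure for these patients.

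The size is unknown. It is zero if no such patients are referred. It is about 1-2 TFI points if 10 % of the sham arm recognise sham and report 10-20 points less improvement, and 2-4 points if the real arm mirrors this. The share, the shift, equal allocation and recognition itself are all assumptions. Taken alone, a bias of this size would rarely decide the result of a trial this small. The case for acting is that the gap is easily closed and its effect would be systematic. It is a cheap improvement to the design and does not show that the blind has failed.

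**What to change.** Add previous tDCS to the exclusion list under Inclusion and exclusion criteria, and ask about it at the ENT consultation where eligibility is already checked. For anyone already enrolled, record previous tDCS at T0 and repeat the TFI comparison without those patients as a sensitivity analysis.

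The cost is one line of text, one question and a short amendment. Trial status says that recruitment has begun but the first randomisations are still to come, so on that timetable the change can be made before it affects the comparison. The downside is slightly fewer eligible referrals and a result that applies to tDCS-naive patients only.

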### Study protocol

#### Tinnitus Retraining Therapy

Every patient will receive approximately six sessions of TRT. The number of sessions will be adjusted to the needs of each patient. The TRT will consist of counselling and adjustment of a noise masker. The patient can try the noise masker at home for 3 months without purchase commitment. During counselling the patient will be educated on the working mechanism of the ear and tinnitus and also learn some coping strategies to deal better with sleeping and concentrations problems.

#### Transcranial Direct Current Stimulation (tDCS)

During every TRT session, the patient will receive tDCS during the counselling. There are two groups: one will receive ‘real’ tDCS and the other will receive ‘sham’ tDCS. The latter is the placebo group. Direct current is transferred by means of 2 saline-soaked pairs of surface sponge electrodes (35 cm^3^) and delivered by a specially developed, battery-driven, constant current neuroConn stimulator (neuroConn, Ilmenau, Germany) with a maximum output of 10 mA. The anode (positive electrode) will be placed on the right DLPFC (Brodmann area 9/46), and the cathode (negative electrode) will be placed on the left upper arm according to the 10–20 international system for electroencephalogram (EEG) electrode placement. The extracephalic placement of the cathode was chosen because of the reduced risk of current flowing from one electrode to the other, and as a consequence, the actual current could stimulate a deeper and wider brain area. Settings for both groups are described in Table 1. For the ‘real’ tDCS group, a constant current of 2 mA will be applied for 20 minutes with a fade-in and fade-out of 10 s. The ‘sham’ tDCS group will receive a tDCS session of only 10 s with a current of 1 mA. Patients in the sham group will experience the same tingling effect at the beginning of the tDCS as those in the real tDCS group, but no real stimulation will take place. Both the patient and investigator are blinded to the intervention type due to a five-digit code that can be entered in the study mode of the tDCS device that will be encoded sham or active tDCS stimulation. The five-digit codes were randomised and supervised by a third party.

**Table 1 Tab1:** Settings for real Transcranial Direct Current Stimulation (tDCS) and sham tDCS

	Real tDCS	Sham tDCS
Current	2 mA	1 mA
Fade in/out	10 s	10 s
Duration	1200 s	10 s

The settings of tDCS are chosen so the patient would not notice a difference and they are blinded for the fact that they are randomised in the placebo or the real treatment group

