#### Side effects

Possible side effects of tDCS are itching or tingling sensation, headache or fatigue and local burns at the position of the electrodes [12].

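### Sham tDCS fades in to half the real current over the same 10 s, so the settings do not support the claim of equal onset tingling

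*Protocol article*

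**What the plan says.** The section on tDCS gives the real arm "a constant current of 2 mA will be applied for 20 minutes with a fade-in and fade-out of 10 s". The sham arm "will receive a tDCS session of only 10 s with a current of 1 mA". Table 1 repeats these settings and lists a 10 s fade in and out for both arms, on a separate row from duration (1200 s real, 10 s sham).

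The same section makes two statements about what the patient feels. One is a flat prediction: "Patients in the sham group will experience the same tingling effect at the beginning of the tDCS as those in the real tDCS group". The other, in the note to Table 1, is an aim: "The settings of tDCS are chosen so the patient would not notice a difference". Concealment of the assignment is handled separately: "Both the patient and investigator are blinded to the intervention type due to a five-digit code", and "The five-digit codes were randomised and supervised by a third party".

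The Side effects section opens with "Possible side effects of tDCS are itching or tingling sensation". The primary outcome section describes the TFI as self-reported, and the Discussion says that comparing sham with real tDCS excludes a placebo effect of tDCS.

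**The concern.** A brief sham works as a placebo by copying the start of real stimulation and then stopping. Here the start is not copied: the fade time is equal, but the target current is halved. Tingling is a sensation that the article itself attributes to tDCS, and the article gives no reason why half the current should feel the same. The five-digit code hides which arm was assigned; it cannot make the two arms feel alike. That job falls to the settings, and the settings differ.

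What is at stake is the reading of the TFI comparison. If some patients can guess their arm from the onset, their expectations can enter a self-reported score and be taken for an effect of tDCS. The onset recurs at each of approximately six sessions. The article presents its double-blind, placebo-controlled design as its advantage, so a sham left unmatched where matching is easy weakens the claim it most relies on.

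**Working it through.** **Inputs** (tDCS section, text and Table 1)

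- Real: 2 mA, fade 10 s in and out, duration 1200 s.
- Sham: 1 mA, fade 10 s in and out, duration 10 s.
- Assumption: linear fades, since the fade shape is not given.

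**Onset.** Ramp = current / fade time.

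- Real: 2 / 10 = 0.2 mA/s.
- Sham: 1 / 10 = 0.1 mA/s.

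| Time from start | Real | Sham |
|---|---|---|
| 1 s | 0.2 mA | 0.1 mA |
| 5 s | 1.0 mA | 0.5 mA |
| 10 s | 2.0 mA | 1.0 mA |

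Real current reaches the sham's maximum at 1 / 0.2 = 5 s and goes on to double it. The 2:1 ratio during the fade-in does not depend on linearity: it holds for any fade shape that is scaled to its peak.

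**Session length.** The real-arm sentence attaches the 20 minutes to the constant current and adds the fades, so duration is time at constant current. On the same layout:

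- Real: 10 + 1200 + 10 = 1220 s.
- Sham: 10 + 10 + 10 = 30 s.

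The text's sham session of 10 s is therefore loosely worded, because the two fades alone take 20 s. After the sham stops, real current runs for a further 1220 - 30 = 1190 s, or about 20 minutes.

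**Charge per session.** Charge = current x duration + 2 x (0.5 x current x fade time).

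- Real: 2 x 1200 + 2 x (0.5 x 2 x 10) = 2400 + 20 = 2420 mC.
- Sham as written: 1 x 10 + 2 x (0.5 x 1 x 10) = 10 + 10 = 20 mC, which is 20 / 2420 = 0.83% of real.
- Sham with the real onset (2 mA, 10 s at constant current): 2 x 10 + 2 x (0.5 x 2 x 10) = 20 + 20 = 40 mC, which is 40 / 2420 = 1.65% of real.

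With the matched sham the ramp is 2 / 10 = 0.2 mA/s in both arms, so the onset is identical by design.

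The article contains nothing from which to derive a perception threshold, a threshold for physiological activity or a bias in TFI points.

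**The case against.** The strongest reply is that unequal current is not unequal sensation. Going from one to the other needs a relation between current and tingling, and the article supplies none. In a parallel-group trial each patient meets only one setting and has no second one to compare it with. This stands, and it limits the point: the equal-sensation statement is unsupported, not shown to be false. A reader might infer that patients will know their arm; the document does not support that.

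A second reply is that the weaker sham may be deliberate. The same section says that sham involves no real stimulation, and a lower current serves that aim. This is a fair trade-off, but a design that makes it should not also assert equal tingling. It is also true that matching the onset removes one cue only, since real current continues long after sham has ended.

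A third reply is that the article never says the code equalises sensation. Agreed; the code is adequate for concealment and is not criticised here.

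On timing, a reader might go further and infer that the sham is undefined: a 10 s session cannot contain two 10 s fades, so the dose might be 5, 10 or 20 mC and the sham could not be reproduced. The document does not support this. Table 1 is named as the specification and lists fades and duration separately, and the real-arm sentence shows how they combine. The 10 mC reading would leave 1190 s at constant current in the real arm, not 20 minutes, and the 5 mC reading drops the fade-out that Table 1 gives the sham. Only 30 s and 20 mC agree with both.

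**Conclusion.** The point holds as a mismatch between a stated claim and the stated settings. Sham current is half of real throughout the fade-in (0.1 against 0.2 mA/s if linear; peak 1 against 2 mA), and nothing in the article supports the statements that the onset feels the same or that patients would not notice. This rests on Table 1 alone; linearity affects the ramp and charge figures but not the 2:1 ratio.

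The consequence is an avoidable risk to patient blinding on a self-reported primary outcome. Its effect on the TFI cannot be sized from the document. It should be fixed because the remedy is cheap and, on the article's own account of trial status, no patient has yet been randomised. The session-length issue is a minor wording correction.

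**What to change.** **Preferred, before the first randomisation.** Set the sham current in Table 1 to 2 mA and describe the sham as a 10 s fade-in to 2 mA, 10 s at 2 mA and a 10 s fade-out (30 s in all), with a fade-in identical to that of the real arm.

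Costs:

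- The third party re-encodes the sham setting in the device. This is about 24 / 2 = 12 codes, assuming the planned 24 patients, one code per patient and 1:1 allocation; the article does not state the code scheme or the ratio.
- A minor amendment is probably needed, since "The study protocol was approved by the ethical committee of the Antwerp University Hospital on 27 October 2014". Recruiting has started, so the first randomisation may have to wait for it.
- Sham charge rises from 20 to 40 mC per session. That 40 mC is inert is an assumption, as it already is for 20 mC.
- Cues after the sham ends remain.

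**If 1 mA is kept.** Withdraw the statement on equal tingling and the Table 1 note on not noticing a difference, state that sham onset is at half the real current, and in the Discussion say that the sham comparison is intended to limit the placebo effect, in place of saying that it excludes it. These are text edits only.

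**In either case.** Replace the 10 s sham session in the text with 10 s at constant current plus a 10 s fade-in and a 10 s fade-out, and note under Table 1 that duration excludes the fades.
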